### Statistical analysis

#### Overall and cancer-specific survival analysis

Overall survival will be analysed using Kaplan–Meier curves, bivariate log-rank tests, and multivariate Cox proportional-hazards models. For cancer-specific and disease-free survival, a competing risk analysis will be performed. The cumulative incidence of CRC-related death in the follow-up will be estimated considering death from other causes as a competing risk, using the method proposed by Kalbfleisch and Prentice [21]. Disease-specific mortality will be compared according to different characteristics, using Gray’s test [22]. Finally, a multivariate analysis will be performed using the model proposed by Fine and Gray [23].

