Kaplan–Meier curves and the Cox proportional hazard models are the statistical methods most commonly used to analyse all-cause mortality in cancer studies, while a competing-risk analysis is preferred to determine cause-specific mortality and its associated factors [7]. However, cure models, which are still not often used, provide an alternative statistical tool to estimate the cure rates of cancer patients and analyse the differences between those individuals who are long and short-term survivors, as well as to identify covariates associated differently with short or long-term progosis [8]. Although some authors have highlighted the usefulness of cure models as an analysis strategy which could provide especially useful information for quantifying the improvement in survival figures in CRC [9], very few publications are available in this regard. These studies show cure rates of around 50% and a median survival rate for uncured patients of about 1 year after diagnosis [9–13]. No such studies have been undertaken in Spain, and furthermore, most of this work has been carried out using population registries and/or do not include clinical information other than the age at diagnosis, sex, and disease stage, and therefore, have not used these models to explore the impact of other covariates on cure rates or survival time.

Data evaluating the long-term health-related quality of life (HRQoL) of CRC survivors are also scarce, although work studying the first 5 years after their diagnosis is more common [14]. Recent work suggests that these patients present a HRQoL similar to that of the general population, although some factors such as intestinal dysfunction can contribute to their deterioration, even 15 years after their initial diagnosis [14]. Furthermore, these results should be contrasted with those obtained in other cohorts and in different locations. Therefore, this study was planned with the aim of determining the long-term prognosis in CRC patients, to characterise long-term survivors and their HRQoL, and demonstrate the utility of statistical cure models in the study of CRC survival. Results from this study may be useful to determine the cure rate (proportion of long-term survivors) in CRC, the survival rates of ‘uncured’ patients and associated factors, and to develop a predictive model to identify long-term survivors from among CRC patients. In addition, it will also allow us to describe HRQoL and the prevalence of symptoms in these patients.

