### Sample size

A cohort of *n* = 1945 incident CRC cases is available from previous research projects. Assuming exposure of 50% and a censored data percentage of 58% [3, 18], this sample size will make it possible to use a Cox regression model to detect significant changes with a hazard ratio (HR) of 1.22 or more (security = 95%; statistical power = 80%). Based on the available survival figures of the *n* = 485 patients included in a previous project for whom baseline HRQoL data are available [17], we estimate that around *n* = 281 patients will still be alive at the time of this proposed study. Assuming loses of around 30%, to estimate HRQoL with 95% confidence and at ±7% precision, we estimate that some *n* = 200 patients will need to be included in this HRQoL sub-project.

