### Measurements

Information about each patient was obtained in our previous studies and is detailed in our other publications [15–17]. This data includes
Sociodemographic data: age at the time of the CRC diagnosis, sex, civil status, and education level.Patient interview data: perceptions and attitudes to the first symptoms of CRC.Personal or family history of cancer or other neoplasms.Comorbidities (Charlson comorbidity index).Disease presentation variables: first symptoms/signs, access to primary and specialised care, first consultation service, examinations and complementary tests prior to the diagnosis, laboratory tests at the time of the diagnosis.Diagnosis and treatment delay.Tumour characteristics at the time of diagnosis: tumour size, site, histological grade, macroscopic appearance, permeation, stage (TNM and Dukes), location of metastases, and infiltration of adjacent organs.Surgical treatment: curative or palliative surgery, type of surgery, access route (laparoscopic vs. open CRC surgery), type of anastomosis, resection of other viscera, resectability, surgical border infiltration, surgical morbidity, and reinterventions and their causes.Chemotherapy or radiation treatments.Complementary tests during follow-up: hospital consultations and physical examinations, laboratory tests, chest X-rays, abdominal ultrasound, colonoscopies, computed tomography, barium enema, and positron emission tomography.

The follow-up data that will be updated in this project include mortality (global and specific), local recurrences, distant metastases, and new-onset neoplasms, together with the date of each of these events. Non-deceased patients will be censored at the end of follow-up or on the latest date for which evidence is available for that patient.

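### Factors for CRC death are compared only on the cumulative-incidence scale, where a covariate's effect on other-cause death can hide or reverse a weak effect on the CRC death rate; add cause-specific hazard models

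*Protocol article*

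**What the plan says.** The protocol article (Statistical analysis, Overall and cancer-specific survival analysis) assigns Kaplan–Meier curves, log-rank tests and Cox models to overall survival. For cancer-specific and disease-free survival it plans a competing-risk analysis. The cumulative incidence of CRC death is estimated with other-cause death as the competing event; "Disease-specific mortality will be compared according to different characteristics" with Gray's test; and "a multivariate analysis will be performed using the model proposed by Fine and Gray". That section names no cause-specific hazard analysis of CRC death.

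The Background gives the purpose of this type of method: "a competing-risk analysis is preferred to determine cause-specific mortality and its associated factors". Objective i asks which variables bear on prognosis, and the Discussion speaks of identifying prognostic factors. Objective iii is predictive.

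The covariates listed under Measurements include age at diagnosis and "Comorbidities (Charlson comorbidity index". The age bands under Cure models run from 15–49 to 80–99.

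**The concern.** Gray's test and the Fine–Gray model work on the subdistribution hazard, which keeps patients who have died of other causes in the risk set for CRC death. Their null hypothesis is equal cumulative incidence of CRC death. A factor that leaves the CRC death rate among living patients unchanged but raises other-cause death lowers the cumulative incidence of CRC death, because fewer patients live long enough to die of CRC. Its sHR is then below 1.

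Age and comorbidity are the covariates for which this matters most, and diagnoses date from 2006 to 2013, so other-cause deaths have had time to accumulate. If sHRs are the only hazard ratios available for CRC death, a reader may take such a factor as protective against dying of CRC, or may miss a modest adverse effect.

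**Working it through.** **1. The plan's own figure.** The Sample size section takes n = 1945, "Assuming exposure of 50% and a censored data percentage of 58" (per cent), and a "hazard ratio (HR) of 1.22 or more (security = 95%; statistical power = 80" (per cent).
- Events: 1945 × 0.42 = 816.9.
- Schoenfeld, two-sided 5%, 80% power: minimum HR = exp[(1.96 + 0.8416)/√(816.9 × 0.25)] = exp(2.8016/14.291) = 1.217, which rounds to 1.22.
- Power at HR 1.22: Φ(14.291 × ln 1.22 − 1.96) = Φ(0.88) = 81%.

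The figure reproduces. It belongs to a Cox model, which the survival section assigns to overall survival, so the 42% need not all be CRC deaths. HR 1.22 is used below only as a benchmark for a modest effect.

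**2. The mechanism by hand.** With constant hazards λ₁ (CRC death) and λ₂ (other causes), the cumulative incidence of CRC death is F(t) = λ₁/(λ₁+λ₂) × [1 − exp(−(λ₁+λ₂)t)]. Assume λ₁ = 0.07 per year in everyone and t = 10 years.
- λ₂ = 0.02: (0.07/0.09)(1 − e^−0.9) = 0.462.
- λ₂ = 0.04: (0.07/0.11)(1 − e^−1.1) = 0.425.
- λ₂ = 0.08: (0.07/0.15)(1 − e^−1.5) = 0.363.

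The ratio of ln(1 − F) to the reference, which approximates the sHR, is 0.89 for a 2-fold and 0.73 for a 4-fold other-cause ratio. The CRC death rate is identical throughout.

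**3. Simulation at the trial's size.** From the article: N = 1945 and 50% exposed. Assumed, because the article gives no such rates:
- administrative censoring at 6–13 years;
- reference other-cause rate 0.02 per year;
- CRC death hazard either constant at 0.07 per year, or cure-type (60% cured, median 1.5 years in the uncured).

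There were 400 runs per scenario, so the Monte Carlo standard error at 5% is √(0.05 × 0.95/400) = 1.1 percentage points. The cause-specific Cox model was compared with the Fine–Gray model, whose score test stands in for Gray's test. No other covariates were included.

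| True HR on CRC death rate | Other-cause ratio | CRC hazard | Cause-specific HR (rejects) | sHR (rejects) |
|---|---|---|---|---|
| 1.00 | 1 | constant | 1.00 (6%) | 1.00 (6%) |
| 1.00 | 1 | cure-type | 1.00 (5%) | 1.00 (5%) |
| 1.00 | 2 | constant | 1.00 (7%) | 0.91 (29%) |
| 1.00 | 2 | cure-type | 1.00 (7%) | 0.96 (11%) |
| 1.00 | 4 | constant | 1.00 (4%) | 0.76 (97%) |
| 1.00 | 4 | cure-type | 1.00 (5%) | 0.88 (38%) |
| 1.22 | 4 | constant | 1.21 (79%) | 0.91 (26%, all protective) |
| 1.22 | 4 | cure-type | 1.22 (82%) | 1.08 (16%) |
| 1.50 | 4 | constant | 1.49 (100%) | 1.11 (30%) |
| 1.50 | 4 | cure-type | 1.50 (100%) | 1.32 (98%) |

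With a true HR of 1.00 and unequal other-cause rates, the sHR rejections are all in the protective direction, except in the cure-type 2-fold case (10 of the 11 percentage points). With equal other-cause rates the two methods agree, which is the expected check.

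With a true HR of 1.5, the average sHR stayed above 1 in every scenario run, including other-cause ratios of 5 and 6 from lower reference rates (0.01 and 0.015 per year). Its lowest value was 1.04 under the constant hazard and 1.28 under the cure-type hazard.

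**The case against.** **These rejections are not false positives on the test's own terms.** This stands. The cumulative incidences truly differ, so Gray's test is right to reject its null. A reader might infer that its type I error is inflated; it is not. The risk lies in reading an sHR as an effect on the CRC death rate, and the survival section does not itself claim that reading.

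**Prognosis and prediction are absolute-risk questions.** This stands in part. The objectives do not mention cause-specific mortality, the quoted purpose comes from a general sentence in the Background, and Fine–Gray suits objective iii. But identifying prognostic factors also invites the question of whether a factor changes the rate of dying from CRC, and the sHR alone does not answer it.

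**Other planned analyses cover the gap.** They do so in part. Mixture cure models estimate covariate effects on cure and on survival of the uncured. Relative survival is set against population mortality by age group, sex and year. The overall-survival Cox model would show a factor that looks protective in Fine–Gray but is harmful overall. None of these, however, is stated as a cause-specific analysis of CRC death. Latency in the cure models is time to death or recurrence with no cause given, and expected mortality does not account for comorbidity.

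**Adjustment would help.** A multivariable Fine–Gray model containing age should remove much of the distortion for factors merely correlated with age, and the unadjusted simulation does not test that model. Adjustment does not change the meaning of the coefficients of age and Charlson themselves, and comparisons by Gray's test are unadjusted.

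**The article is condensed.** A fuller analysis plan may already contain cause-specific models, which would close the point. The article does, however, allocate methods to endpoints explicitly, and gives Cox and log-rank in that section to overall survival alone.

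**Conclusion.** The point holds as a conditional one. Within the cancer-specific section, the only named comparisons for CRC death mix the CRC death rate with other-cause mortality. For covariates strongly tied to other-cause death and with a null or weak effect on the CRC death rate, the sHR can fall below 1 or conceal a modest effect. With no effect on the CRC death hazard and a 2- to 4-fold other-cause ratio, the sHR is about 0.76–0.96 with 11–97% rejection. At a true HR of 1.22 and a 4-fold ratio, power to detect harm drops from about 80% to 0% (constant hazard) or 16% (cure-type).

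All of this rests on assumed event rates. The lower end applies when CRC deaths come early, and the median of about 1 year in uncured patients cited in the Background points that way.

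A reader might go further and infer that age and comorbidity will look protective, or that the whole plan lacks any disease-related view of covariates. The documents support neither. Strong effects keep their direction on average, although the constant-hazard case still loses much of its power at HR 1.5. The cure models, relative survival and overall-survival Cox model give partial cover. Nor is Fine–Gray wrong in itself; the weakness is relying on it alone for associated factors. This is a worthwhile, low-cost improvement, not a flaw that invalidates the plan.

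**What to change.** - Keep cumulative incidence, Gray's test and Fine–Gray for absolute risk and prediction.
- Add cause-specific Cox models for CRC death and for other-cause death, each censoring the other event, and likewise for recurrence.
- Report cause-specific and subdistribution hazard ratios side by side.
- Base statements about factors associated with the CRC death rate on the cause-specific hazard ratios, and describe sHRs as effects on cumulative incidence.

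The cost is about one sentence in the analysis section and a few routine models. Overall and cause-specific mortality, recurrences and their dates are already to be updated under Measurements, so no new data are needed. The downside is a second set of hazard ratios to present and interpret.

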#### Relative survival

Relative survival will be estimated as the ratio of observed survival of CRC patients and the survival that would have been expected if the patients had had the same mortality rate as the general population. The expected survival will be estimated from the population mortality rates estimated for the health area by age group, sex, and study year, using the Ederer II method [24]. Following other publications, the ‘statistical cure’ point will be defined as the point at which the relative survival curve plateaus, e.g., when the patients remaining alive experience the same mortality rate as the age and sex-matched population without cancer [9–13]. Thus, the value at which the plateau is achieved will provide an estimation of the curation rate.

#### Cure models

The cure rate and ‘latency’ (time to death or recurrence) will be estimated using parametric and semi-parametric mixture cure models [8]. For parametric models, logistic regression will be used to analyse the cure fraction and the Weibull distribution will be used to model the survival probability of uncured patients. For semi-parametric analysis, long-term survival will be modelled using a Cox proportional-hazards model. The following results will be obtained from the estimates of the models, (a) the cure rate; (b) relative survival curves for all the patients and for uncured patients; (c) median survival rates in uncured patients; and (d) the timepoint at which 90% of the uncured patients have died. Estimates will be obtained for each sex and CRC location (colon vs. rectum), according to age (15–49, 50–59, 60–69, 70–79, and 80–99), and year of diagnosis. Using these models, the effect of different covariates on the cure rate and survival of the uncured patients will be determined independently. The parameters of the model will be estimated using the maximum likelihood method.

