## Discussion

CRC is a major public health problem worldwide and is one of the most common tumour types in terms of its incidence and associated mortality rates [1]. Advances in the diagnosis and treatment of CRC has caused its mortality rates to decrease in recent years, thus increasing the number of long-term CRC survivors [3]. These survivors experience the normal issues related to aging, along with the physical and emotional effects of a cancer diagnosis and of its treatments [25]. Therefore, one goal remains further improvement of the probability of ‘curing’ this disease while also improving the life expectancy for these cured patients.

Thus, large epidemiological studies are important to check the effects of diagnosis and treatment improvements in terms of patient survival, to identify prognostic factors, and to detect subgroups who could need more frequent follow-up surveillance. Therefore, the primary endpoint of this proposed study will be to provide an accurate, updated estimation of long-term survival in CRC patients, as well as to identify variables that may be associated with the probability of a cure and with survival time in uncured patients.

Traditional statistical methods (such as Kaplan–Meier curves or the Cox proportional hazards model) commonly used to estimate survival in CRC patients, implicitly assume that all patients with the same global diagnosis of CRC are at risk of developing the event of interest (e.g., death from the tumour) if they are followed for a sufficiently long period of time. This hypothesis is reasonable when overall mortality is analysed, but falls short when analysing specific-cause mortality or disease-free survival because some patients will never die from the CRC cancer or suffer a recurrence of the tumour. Therefore, alternative survival models taking this into account should be considered.

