Statistical cure models could be a useful alternative in this context, even though they are not often currently used in clinical research [26]. Cure models assume that a fraction of the patients will be cured by the treatment and will never be at risk for suffering an event related to the specific disease again (e.g., CRC death, recurrence, or metastases). Therefore, these models might provide a better estimation of the ‘cure fraction’ while also modelling the average time to the occurrence of a new event among uncured patients as well as associated prognosis factors. These models therefore allow the clinical determinants of the cure and the variables associated with survival to be analysed [27].

To the best of our knowledge, this is the first study in Spain employing cure models to analyse the long-term prognosis of CRC patients. Furthermore, no other published studies have evaluated the impact of clinical variables other than age, sex, disease stage, or location on long-term CRC survival by using a similar methodology. The research published to date are mainly cancer-registry population studies that do not include clinically important variables such as those registered in hospital-based cohort studies like this one. Other strengths of this project are its relatively large sample size and the long-term follow-up periods considered.

Health care for long-term survivors must include strategies not only for the early diagnosis of recurrences and new neoplasms, but also to detect the long-term medical and psychological effects of cancer diagnosis and treatments [25]. Thus, characterisation of long-term survivors and analysis of their outcomes will help researchers to assess the adequacy of the medical care provided to them and to optimise the health resources invested in these patients. The secondary aims of this project will be to provide information on the symptoms and HRQoL of long-term CRC patients. These results will allow us to confirm whether, as other authors have indicated, HRQoL returns to normal 1 year after diagnosis [28]. This data could be important to CRC patients, for example, in planning scheduled follow-up visits to screen not only for medical issues, but also for the late effects of treatments on patient HRQoL and symptoms.

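### The event and survival scale of the mixture cure models conflict; fitted as written, they would count deaths from other causes as failures to cure in older patients

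*Protocol article*

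**What the plan says.** All references are to the protocol article.

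- **Cure models, event.** The latency is described as "time to death or recurrence) will be estimated using parametric and semi-parametric mixture cure models". Death is not restricted by cause.
- **Cure models, components.** For the parametric model, "logistic regression will be used to analyse the cure fraction and the Weibull distribution will be used to model the survival probability of uncured patients". The semi-parametric version is described thus: "long-term survival will be modelled using a Cox proportional-hazards model". Nothing is said about expected mortality or deaths from other causes.
- **Cure models, outputs.** The models are to supply (a) the cure rate, "b) relative survival curves for all the patients and for uncured patients", (c) median survival of the uncured and (d) the time by which 90% of the uncured have died. Estimates are given by age band, including 70–79 and 80–99, and covariate effects on cure and on survival of the uncured come from these models.
- **Relative survival.** Expected survival comes from "population mortality rates estimated for the health area by age group, sex, and study year, using the Ederer II method". Statistical cure is the point where the relative survival curve flattens, and the plateau height estimates the cure rate.
- **Discussion.** Of the assumption that every patient is at risk of the event, it says: "This hypothesis is reasonable when overall mortality is analysed, but falls short when analysing specific-cause mortality or disease-free survival". Cured patients are those who "will never be at risk for suffering an event related to the specific disease again", with CRC death, recurrence and metastases as examples.
- **Measurements.** Overall and specific mortality, recurrences and metastases are all collected with dates.

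**The concern.** A mixture cure model needs an event that cured patients never have. Death from any cause is not such an event, and the Discussion says as much. Fitted to all-cause death without an expected hazard, the model has no true plateau to find. It reads the number still alive late in follow-up as the cure fraction, and that number falls with age whatever the cancer does.

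Objective ii (the cure rate, survival of the uncured and the factors associated with each) is at stake. The Discussion also places the variables associated with cure and with survival of the uncured in the primary endpoint. Any covariate tied to non-cancer death, such as age, sex or the Charlson index, could appear to act on cure when it does not. The relative survival plateau gives a second cure rate, but no regression is stated for it, so the covariate effects rest on the cure models.

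**Working it through.** **1. The plan's own figure.** The only power figure is a detectable HR of 1.22 for Cox regression (Sample size). Events = 1945 × (1 − 0.58) = 816.9. Schoenfeld's formula with 50% exposed needs 4(1.960 + 0.842)² / (ln 1.22)² = 794 events; 816.9 events give 81.1% power. The figure reproduces. It concerns the Cox model; none is given for the cure models.

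**2. Can one event and scale satisfy the text?**

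| Reading of the event | What fits | What conflicts |
|---|---|---|
| Any death or recurrence, no expected hazard | The latency wording and the named components | Cannot give relative survival; contradicts the Discussion's definition of cure |
| Any death or recurrence, relative survival scale | Output (b), the plateau definition | Population rates count deaths only, so the composite has no expected counterpart |
| CRC-specific events only | The Discussion | Output (b) would not be relative survival; death in the latency wording is unqualified |

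Outputs (c) and (d) concern death alone, while the stated latency also contains recurrence.

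**3. Size under the literal reading.** The correct structure for all-cause death is S(t) = S*(t)[π + (1 − π)Su(t)], where S* is expected population survival. Leaving out S* forces its decline into π and Su.

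Inputs from the article (Background): cure about 50%, median survival of the uncured about 1 year.

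Assumed, not in the article: exponential latency; follow-up uniform over 6–13 years; Gompertz background hazard of 0.018 per year at age 70, rising by a factor exp(0.095) per year of age; no separate recurrence process.

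With 20,000 patients per age, a logistic–Weibull mixture was fitted by maximum likelihood in three ways. True cure is 0.50 at every age.

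| Age | Background hazard at diagnosis | Cure: any death, no background | Cure: CRC events only | Cure: any death, background in likelihood | Uncured median (years): any death, no background |
|---|---|---|---|---|---|
| 45 | 0.0017 | 0.488 | 0.501 | 0.503 | 1.06 |
| 55 | 0.0043 | 0.463 | 0.501 | 0.503 | 1.13 |
| 65 | 0.0112 | 0.399 | 0.503 | 0.502 | 1.38 |
| 75 | 0.0289 | 0.231 | 0.501 | 0.495 | 2.01 |
| 85 | 0.0748 | 0.029 | 0.500 | 0.497 | 2.37 |

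Hand check at age 75: the cumulative background hazard to 13 years is (0.0289/0.095)(e^{1.235} − 1) ≈ 0.74, so S* ≈ 0.48. Almost no uncured patients remain by then, so all-cause survival is about 0.50 × 0.48 = 0.24, close to the fitted 0.231.

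**4. Sensitivity.** The assumptions were varied: uncured median 2 years, follow-up 4–11 years and, for ages 65 and over, hazard at age 70 of 0.012 or 0.025. The literal fit ranged over 0.47–0.49 at 45, 0.45–0.47 at 55, 0.35–0.44 at 65, 0.16–0.32 at 75 and 0.00–0.12 at 85. Both alternative fits stayed at 0.49–0.51 throughout. A second simulation (40,000 per age band, follow-up 5–13 years, its own assumed Gompertz background) gave 0.46, 0.38, 0.21 and 0.01 for ages 50–59, 60–69, 70–79 and 80–91, and 0.49–0.50 with the background hazard included.

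**5. Covariate distortion.** Cure does not depend on age here. Yet the literal fits at 75 and 45 imply an odds ratio for cure of (0.231/0.769)/(0.488/0.512) ≈ 0.32. Sex and comorbidity were not simulated; the same mechanism applies to them so far as they affect non-cancer death.

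**The case against.** A reader might infer that the plan leaves background mortality out of its cure models and that the cure rate is therefore biased. The article does not support that. It never says that expected mortality is excluded. Asking for relative survival curves presupposes it, the preceding section supplies it, and the Discussion ties cure to disease-specific events. The authors may well intend a relative-survival or cause-specific model. This stands, and it makes the bias conditional.

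The latency phrase could also mean two outcomes, death and recurrence, modelled separately. That is the most coherent reading. But the text attaches one cure rate and one set of outputs to both model types, leaves death unqualified, and states nothing that would bring expected mortality into the Cox version.

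A condensed article may leave the likelihood to a fuller document. That is fair for technical detail. Here, though, the event, the components and the outputs are all stated and do not agree.

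Two further readings go too far:

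- That the Cox model is put on the wrong part of the mixture. The sentence is loose, but after logistic regression and Weibull have been assigned their parts, Cox replacing Weibull for the uncured is the ordinary reading.
- That recurrence is undefined for patients with metastatic disease or palliative surgery. An article may leave that out; stage and type of surgery are recorded.

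Nor is the whole primary endpoint affected. Long-term survival is also estimated by Kaplan–Meier, competing-risk and relative survival methods, which do not depend on this.

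**Conclusion.** The point holds as a contradiction in stated rules: the event and survival scale of the cure models cannot be reconciled across the Cure models, Relative survival and Discussion sections. It does not hold as a demonstrated bias.

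If the models are fitted to death from any cause with no expected hazard, the cure fraction is underestimated and median survival of the uncured overestimated. The loss is small below 60, material in the 60s and severe in the 70–79 and 80–99 bands that the plan will report. The direction follows from the model's structure. The sizes depend on assumed population mortality, follow-up and latency, and leave recurrence out of the event. The relative survival plateau remains an independent estimate of the overall cure rate, but it does not protect the analysis of covariates. The conflict should be resolved before the cure models are fitted.

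**What to change.** Rewrite the Cure models paragraph so that each model has one event and one scale.

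1. **Death from any cause.** Fit a relative-survival mixture cure model, S(t) = S*(t)[π + (1 − π)Su(t)], with the health-area mortality rates already planned under Relative survival in the likelihood. Take outputs (a)–(d) from this model.
2. **Semi-parametric model (logistic cure probability, Cox latency of the uncured).** Use CRC-specific events only, with deaths from other causes censored, and do not label its curves relative survival. This relies on the recorded cause of death and on other-cause death being independent of the CRC process given the covariates; say so.
3. **Recurrence.** Analyse it as a separate outcome, not as part of the relative-survival event.

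The cost is one rewritten paragraph and slightly more analysis work. The population rates and cause of death are already planned, so no new data are needed.
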